### Covariates

Parents will report on socio-demographic factors (age, sex, and race/ethnicity), and adolescents will report on pre-surgery pain severity and interference using the 7-day recall version of the Brief Pain Inventory [43].

### Treatment variables

*Treatment satisfaction and acceptability.* Adolescents and parents will complete the Treatment Evaluation Inventory Short Form, a 9-item self-report measure assessing perceptions of acceptability and satisfaction with the pre- and post-operative treatment content and approach [44], directly after each treatment phase. Select items on this measure were adapted to be specific to treatment of pediatric postsurgical pain. Items are rated on a 5-point scale (1 = strongly disagree, 5 = strongly agree) and summed to create a total score, with higher scores indicating higher levels of treatment satisfaction and acceptability.

*Treatment experience*. Adolescents and parents will complete a Treatment Experience Survey developed for this study concerning whether they experienced negative effects of study participation (e.g., worrying about pain, overwhelmed with treatment assignments, tension at home) and rate the level of discomfort experienced (0 = “did not affect me/my teen at all” to 3 = “affected me/my teen very negatively”). The number, type, and severity of negative experiences will be summarized. Participants will also report unrelated adverse events via free text response.

*Concomitant therapy.* Parents will report on additional health services accessed for pain or anxiety management during the pre- and post-operative treatment phases. Responses will be coded into a binary variable indicating whether concomitant therapy was accessed (yes/no).

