### Trial design and randomization

This study will utilize a single-blinded, randomized 2 × 2 factorial design (see Fig. 1). Block randomization will be used to allocate participants to one of four arms with random block sizes, stratified by participant sex. The randomization allocation table will be implemented using the REDCap randomization framework using an allocation ratio of 1:1:1:1 and will occur directly before treatment assignment. The randomization process will be overseen by an independent statistician, who is not involved with study procedures, including participant recruitment, intervention assignment, or any other forms of participant contact. Randomization results will only be directed to the study coordinator, who will assign participants to the intervention groups. All other study staff including the trial investigators, and data analyst will be blinded to treatment assignment. Care providers will not be informed of treatment assignment, and participation in the study will not affect clinical care. Participants may therefore engage in any other intervention or treatment (e.g., counseling, physical therapy). In the unlikely event of an adverse event, unmasking would be permissible.

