### Criteria for discontinuing allocated interventions

Adverse events, if any, are expected to be minor and there are no planned criteria for discontinuing or modifying allocated interventions. Participants will be removed from the study by the trial investigators if they are non-compliant with the pre-randomization baseline assessment, undergo a second major surgery (e.g., repeat spinal fusion surgery) or are diagnosed with a new complex medical condition (e.g., cancer) during the study time frame. Timepoints prior to the new presentation of exclusionary condition will be analyzed. Participants may withdraw from the study and intervention at any time.

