### Oversight and monitoring

Study monitoring to ensure proper consenting and assenting procedures, maintenance of IRB approval, intervention implementation, and security of databases will be conducted by Trial Innovation Centers (TICs) including the University of Utah DCC and Duke/Vanderbilt Clinical Coordinating Centers (CCCs). The DCC will work closely with research coordinators and principal investigators to oversee study data management. In addition, an independent Data and Safety Monitoring Board (DSMB) comprised of experts from pediatric psychology, behavioral interventions, and statistics will convene biannually in an open session followed by a closed session to review study progress, data, and participant safety. Authorship will be determined in accordance with the HEAL Initiative Publication Policy.

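### Families' own view of causality decides how a harm is recorded: events they call unrelated get no rating and fall outside the stated harms summary

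*Protocol article*

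**What the plan says.** The paragraph on treatment experience, under Treatment variables in the protocol article, sets out how harms are collected. "Adolescents and parents will complete a Treatment Experience Survey developed for this study", which covers "whether they experienced negative effects of study participation (e.g., worrying about pain, overwhelmed with treatment assignments, tension at home". Respondents then "rate the level of discomfort experienced" on a four-point scale from 0 to 3. The stated analysis is: "The number, type, and severity of negative experiences will be summarized". A second channel follows: "Participants will also report unrelated adverse events via free text response".

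Three other places touch on safety:
- The section on discontinuing interventions gives the authors' expectation and the absence of stopping rules: "Adverse events, if any, are expected to be minor and there are no planned criteria for discontinuing or modifying allocated interventions".
- Trial design and randomization: "In the unlikely event of an adverse event, unmasking would be permissible".
- Oversight and monitoring: an independent board meets twice a year "to review study progress, data, and participant safety".

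**The concern.** A comparison of harms between randomised arms is sound when events are collected in the same way whatever anyone believes caused them, with causality judged afterwards. Here the order is reversed: the family's judgement of cause comes first, and it determines whether the event is rated and whether it falls under the stated summary.

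Families are poorly placed to make that judgement. The adolescent has just had major spinal surgery, which offers a ready explanation for almost any setback. The education website also exists partly so that allocation can be masked, so families are asked to attribute events to a programme whose active or control status is meant to be unclear to them.

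At stake is what the rated summary measures. As described, it counts events that families attribute to the study, which is not the same as the events that occurred in each arm.

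**Working it through.** The article gives no harms rate, safety sample size or precision target, so there is no figure to reproduce and no arithmetic applies. The check is a side-by-side reading of the sections that mention adverse events, negative effects, unmasking or safety review.

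**Step 1. Compare the two channels in the treatment experience paragraph.**

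| | Channel 1 | Channel 2 |
|---|---|---|
| What is asked for | Negative effects of taking part | Adverse events labelled unrelated |
| Who sorts the event | Adolescent or parent | Participant |
| Form | Survey with a rating | Free text |
| Rating | 0 to 3 | None stated |
| Stated summary | Number, type, severity | None stated |

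The only thing that separates the columns is the respondent's view of cause.

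**Step 2. Follow one event through both.** Suppose an adolescent makes an emergency visit during the post-operative phase. If the family links it to the programme, it enters channel 1, is rated, and falls under the summary. If the family blames the operation, the same event enters channel 2 as unrated text, outside the stated summary. The event and the arm are the same, but the record differs.

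**Step 3. Ask what a later document could repair.** Free text can still be coded, reviewed for relatedness and tabulated by arm, and a full protocol or analysis plan may provide for that. A 0 to 3 rating that was never requested cannot be supplied afterwards. This part is fixed at collection.

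**Step 4. Ask what else in the plan would catch the event.**
- Table 3 has anxiety and depression scales, a brief anxiety and depression screen for adolescent and parent, and a sleep quality scale, all at baseline, 3 months and 6 months. None asks the respondent about cause.
- The Brief Pain Inventory, including interference with mood and sleep, is completed daily for 14 days after discharge and for 7 days at 3 and at 6 months.
- Secondary analyses compare anxiety, depressive symptoms and sleep quality between arms at 3 months.
- Parents report extra health services used for pain or anxiety in both treatment phases, reduced to yes or no.

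A lasting worsening of mood, sleep, anxiety or pain would therefore probably show on these scales. Their recall periods run from 24 hours to one month, and they yield scores, not event records. An emergency visit, an admission or a short episode between assessments would not reliably appear. That is the gap that remains.

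**The case against.** The strongest reply is that the survey item itself is not shown. The word *unrelated* may be the authors' shorthand for anything outside the negative-effects list, and the actual form may already ask neutrally. This cannot be excluded, and the article says the forms are available on request. But the sentence as printed has participants reporting unrelated events, and the rating and summary are attached to the other channel.

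The reply also holds that coding, causality review and tabulation are commonly left to the full protocol or analysis plan. That stands, and their absence here is no finding. It does not reach the rating or the prompt, which are fixed when the family answers.

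A reader might infer more than the article supports:
- *That these events are lost.* They are recorded as free text, and nothing says the text is left uncoded or unreviewed.
- *That the monitoring board sees only the events that families attribute to the study.* Its remit is study data and participant safety, with no restriction to the rated survey.
- *That nothing is asked after the post-operative phase ends at about week 7.* The timing directly after each phase belongs to the satisfaction questionnaire; none is given for this survey. Removal for a second major surgery or a new complex condition also implies some ascertainment throughout the study.
- *That the comparison between arms is necessarily biased.* If families in every arm attribute the same fraction p of events, expected rated counts become pE1 and pE0, and their ratio stays E1/E0. Distortion of that ratio needs p to differ by arm, and the article gives no figure for p.
- *That the listed examples favour one arm.* Being overwhelmed by assignments may suit the CBT parent lessons better, but it is one of three examples, and the tasks on the education site are not described in full.

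**Conclusion.** The concern holds as a modest defect in how harms are collected. Events that families attribute to the study are rated and summarised; other events are kept as unrated text, with no summary stated. A programme-related event put down to surgery would be on file, but without a rating and outside the stated summary. The consequence is largest for discrete or transient events, since the symptom scales give attribution-free cover for mood, sleep, anxiety and pain at 3 and 6 months.

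Its size cannot be expressed as a number from this article. Sample size, error rates and the efficacy analyses are untouched. The conclusion assumes that the survey follows the article's description. If the form already asks for all events neutrally, what remains is the missing rating and the narrow summary statement.

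**What to change.** First check the survey form against the article's sentence. Then:

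1. Word the free-text item neutrally, for example: *any new or worse health problem, including an emergency visit or hospital admission, whether or not you think the study caused it*.
2. Rate each such event on the existing 0 to 3 scale. That scale asks how much the person was affected, so it works without any judgement of cause.
3. Have an existing investigator assign relatedness afterwards. The article already keeps trial investigators masked to allocation.
4. Summarise all events by allocated arm regardless of attribution, with the related subset shown separately.

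The cost is a change of survey wording and some coding time for existing staff. The real downside is that more expected post-surgical events will be reported and need coding in every arm. Recruitment was planned from December 2020 to December 2023, so a change made around the April 2021 protocol version would reach most participants. For families already surveyed, the free text can be coded and tabulated, but ratings for those events will be missing, and the report should say so.

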### Data management

Research data will be stored on a Health Insurance Portability and Accountability Act (HIPAA)-compliant secure server hosted, managed, and monitored by the University of Utah Data Coordinating Center (DCC), with daily backups, and will be deidentified at the earliest possible opportunity. Participant contact information will be stored separately in secure, password-protected databases stored locally on HIPAA-compliant servers at Seattle Children's Research Institute and the University of Washington Institute of Translational Health Sciences. Databases will be linkable only by a unique study identifier.

### Data analysis

The primary analyses will be intent-to-treat analyses which will include all participants randomized, with adolescent as the unit of analysis. All regression analyses will adjust for a priori identified demographic variables (age, sex, race/ethnicity), prognostic covariates (pre-surgery pain intensity), and study site. Separate models will be conducted to analyze pain severity and pain interference (primary outcomes), as assessed by the BPI. For multi-item instruments, published rules on treatment of missing data will be followed where available; otherwise, hot deck imputation will be used for individual items for less than 20% missing data. There are no interim analyses planned.

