## Abstract

**Background:**

Spinal fusion surgery is associated with severe acute postsurgical pain and high rates of chronic postsurgical pain in adolescents. Psychological distress, sleep disturbance, and low pain self-efficacy predict higher acute pain and likelihood of developing chronic postsurgical pain. Interventions targeting baseline psychosocial risk factors have potential to interrupt a negative trajectory of continued pain and poor health-related quality of life (HRQL) over time but have not yet been developed and evaluated. This randomized controlled trial will test effectiveness of a digital peri-operative cognitive-behavioral intervention (SurgeryPal^TM^) vs. education-control delivered to adolescents and their parents to improve acute and chronic pain and health outcomes in adolescents undergoing spine surgery.

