## Introduction

### Background and rationale

Spinal fusion surgery is one of the most frequently performed major musculoskeletal surgeries in children and adolescents, with an estimated 12,600 procedures performed in the USA annually [1]. The majority of pediatric spinal fusion surgeries are performed for idiopathic spinal deformities (e.g., scoliosis, spondylolisthesis), with adolescent idiopathic scoliosis being the most common. Spinal fusion results in intense acute postsurgical pain and high rates of chronic pain, with 80% of otherwise healthy adolescents reporting moderate to severe acute pain [2–4], and up to half reporting persistent pain 6–12 months post-surgery [5–7].

Recent biopsychosocial models conceptualize transition from acute to chronic pain as a complex interplay of biological, psychosocial, and sensory mechanisms [8, 9] and highlight the pre- and post-surgery phases as potential opportunities to intervene to prevent chronification of pain [10]. However, there is a lack of understanding of how to halt the transition from acute to chronic postsurgical pain (CPSP). In adolescents, psychosocial risk factors including anxiety and depressive symptoms, sleep disturbance, low pain self-efficacy, and high parent anxiety are associated with poorer pain and health outcomes at both short- and long-term follow-up after surgery [6, 11–15]. Moreover, adolescents who experience severe acute postsurgical pain are at elevated risk for developing CPSP, a condition marked by chronic pain which impacts health-related quality of life (HRQL) after surgery [14]. Interventions targeting baseline psychosocial risk factors may reduce acute postoperative pain and have potential to interrupt a negative trajectory of continued pain and poor health outcomes.

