### Secondary outcome measures

Table 3 provides details on the secondary outcome measures.

**Table 3 Tab3:** Secondary outcomes measures

Measure	Description	Respondent	Time point			
			T1	T2	T3	T4
Pediatric Quality of Life Inventory - Short form, acute version^a^ [32, 33]	15-item measure assessing health-related quality of life (HRQL) over the last 7 days across the following domains/subscales: physical health, psychosocial health, and total HRQL, reported on a 5-point Likert scale.	Adolescent	✔		✔	✔
Opioid use [30]	2 items on the BPI assessing daily opioid use and pain relief from medications. Acute opioid use will be calculated as the number of days of opioid use during 14 days daily monitoring (T2).	Adolescent	✔	✔	✔	✔
NIDA-Modified ASSIST Tool^a^ [34, 35]	15-item measure assesses alcohol, smoking, substance, and opioid misuse in the past 2 weeks; additional questions about reasons for misuse (e.g., to treat pain, to get high, etc.) and source of opioids (e.g., prescription, from a friend or relative) will be used from the National Survey on Drug Use and Health [36].	Adolescent	✔		✔	✔
PROMIS Pediatric Anxiety SF8a [37]	8-item measure used to assess adolescent self-reported anxiety. Adolescents endorse frequency of fear, anxiety, hyperarousal, and somatic symptoms experienced in the prior 7 days, on a 5-point Likert scale.	Adolescent	✔		✔	✔
PROMIS Pediatric Depression SF8a [37]	8-item measure assess depressive symptoms. Frequency of negative mood, negative views of self, decreased positive affect, and decreased engagement in the prior 7 days reported on a 5-point Likert scale.	Adolescent	✔		✔	✔
Patient Health Questionnaire-4^a^ [38]	4-item screening measure of general anxiety and depressive symptoms experienced in the preceding 2 weeks by the respondent.	Adolescent, parent	✔		✔	✔
Pain Catastrophizing Scale – Child Version^a^ [39]	13-item measure that assesses child pain catastrophizing. Adolescents report frequency of symptoms of rumination, magnification, and helplessness experienced when in pain using a 5-point Likert scale.	Adolescent	✔		✔	
Pain Catastrophizing Scale – Parent Version^a^ [40]	13-item measure that assesses parents’ symptoms of rumination, magnification, and helplessness, in response to their child experiencing pain, on a 5-point Likert scale.	Parent	✔		✔	

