Adolescent Sleep Wake Scale 10^a^ [41]	10–item measure of self-reported sleep quality in preceding month, including going to bed, falling asleep, reinitiating sleep, and returning to wakefulness using a 6-point Likert scale; four additional items from the Children’s Report of Sleep Patterns (CRSP) measure querying bedtime and wake time on weekdays and weekends will assess sleep duration [42].	Adolescent	✔		✔	✔
Patient Global Impression of Severity Scale^a^	1-item assessing adolescent’s self-reported global impression of pain severity in the past 24 h (T2) or past week (T3 and T4), with response options “None” (0), “Mild” (1), “Moderate” (2), and “Severe” (3)	Adolescent		✔	✔	✔

^a^Pediatric core Common Data Element (CDE) measures for the Help End Addiction Long Term (HEAL) Initiative. PROMIS, Patient-Reported Outcome Measurement Information System; NIDA, National Institute on Drug Abuse; ASSIST, Alcohol, Smoking and Substance Involvement Screening Test

T1, pre-randomization baseline; T2, acute outcomes daily for 14 days post-hospital discharge; T3, chronic outcomes at 3 months post-surgery; T4, final follow-up at 6 months post-surgery

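### The primary pain models adjust for no baseline psychosocial score, although the protocol names such factors as predictors and collects them before randomisation; a little precision is forgone, without bias

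*Protocol article*

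**What the plan says.** The protocol article fixes the adjustment set in its Data analysis section: "All regression analyses will adjust for a priori identified demographic variables (age, sex, race/ethnicity), prognostic covariates (pre-surgery pain intensity), and study site". The Covariates section is consistent with this. Apart from socio-demographics it lists only baseline pain: "adolescents will report on pre-surgery pain severity and interference using the 7-day recall version of the Brief Pain Inventory". Neither place mentions a psychosocial score.

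Two other places describe psychosocial factors as prognostic. The abstract says: "Psychological distress, sleep disturbance, and low pain self-efficacy predict higher acute pain and likelihood of developing chronic postsurgical pain". The introduction (Background and rationale) says that "anxiety and depressive symptoms, sleep disturbance, low pain self-efficacy, and high parent anxiety are associated with poorer pain and health outcomes", and it refers to both short-term and long-term follow-up.

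Table 3 (Secondary outcome measures) ticks T1, defined as the baseline before randomisation, for these instruments:
- PROMIS Pediatric Anxiety, an "8-item measure used to assess adolescent self-reported anxiety"
- PROMIS Pediatric Depression, an "8-item measure assess depressive symptoms"
- the Adolescent Sleep Wake Scale, a "measure of self-reported sleep quality in preceding month"
- the PHQ-4, completed by adolescent and parent

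Table 3 lists no measure of pain self-efficacy, so that factor could not be adjusted for. Randomisation is stratified by sex only. The exploratory analyses use change from T1 in sleep, anxiety and depression as possible mediators. Nowhere do the T1 values serve as covariates in the primary pain models.

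**The concern.** The trial rests on the premise that these baseline factors drive pain after spinal fusion. If so, their T1 values explain part of the variation in pain severity and interference that has nothing to do with the allocated arm. Leaving them out keeps that variation in the error term. The confidence intervals for the primary comparisons are then wider than the collected data require.

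The stake is largest where margin is smallest. Hypothesis 3 compares both phases with a single active phase as well as with education alone. The sample size section gives no separate calculation for that increment, which could plausibly be smaller than the 1.0 point planned for the chronic outcomes. The covariates also have to be named before results are seen, because adding them afterwards would look data-driven.

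**Working it through.** **Inputs from the protocol article.** Chronic primary outcomes: difference 1.0, SD 1.8, two-sample t test, 35 per arm for 80% power. Complete sample 400 in four equal arms, so 100 per arm.

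**Assumptions.** Two-sided alpha of 0.05, since the article states none. The value 1.8 is treated as the residual SD under the planned covariates. R2 is the share of that residual variance explained by the psychosocial scores, set at 5%, 10% and 15% because the article gives no figure.

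**Step 1, the plan's own figure.** n per arm = 2 x (1.96 + 0.84)^2 x 1.8^2 / 1.0^2 = 51, or 52 with the t distribution. One-sided 0.05 gives 41. The stated 35 is not reproduced. That is a separate matter and does not affect this point, because 100 completers per arm exceed all of these figures.

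**Step 2, precision as planned.** SE = 1.8 x sqrt(2/100) = 0.255. Power for 1.0 is 97.4%. The difference detectable with 80% power is 2.80 x 0.255 = 0.71.

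**Step 3, precision with the extra scores.** SE = 0.255 x sqrt(1 - R2).

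| Assumed extra R2 | SE | Power, difference 1.0 | Power, difference 0.7 (assumed) | Power, difference 0.5 (assumed) | Detectable at 80% |
|---|---|---|---|---|---|
| 0 | 0.255 | 97.4% | 78% | 50% | 0.71 |
| 5% | 0.248 | 98.0% | 80% | 52% | 0.70 |
| 10% | 0.241 | 98.5% | 82% | 54% | 0.68 |
| 15% | 0.235 | 98.9% | 84% | 56% | 0.66 |

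For Hypothesis 2, which uses about 200 completers, the gain equals 200 x (1/(1 - R2) - 1) = about 11, 22 or 35 extra completers.

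**Step 4, chance imbalance.** The standardised baseline difference between arms of 100 has SD sqrt(2/100) = 0.141, so 95% of such differences lie within 0.28 SD. For one score with an assumed correlation of 0.3 with the outcome, the 95% limit of the shift is 1.96 x 0.3 x 1.8 x 0.141 = 0.15 points. With 200 per group and the same SD it is 0.11.

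This shift is already part of the ordinary SE. Its SD is 0.3 x 0.255 = 0.0764, with variance 0.0058, which is 0.3^2 = 9% of 0.255^2 = 0.0648. It is therefore the same loss as in step 3, not a further one.

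**Step 5, validity.** In a simulation of 100 v 100 with no treatment effect (4,000 runs per setting), the covariate explained 5% or 15% of variance. Type I error was 4.6% and 4.8% without adjustment, and 4.8% and 5.1% with it. The mean estimated difference was within 0.01 points of zero in every case.

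**Scope.** These figures apply to a linear 100 v 100 comparison (Hypotheses 2 and 3). They do not carry over to Hypothesis 1, which pools arms to about 200 v 200 and uses an exponential-decay mixed model and a GEE model.

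**The case against.** The strongest reply is that nothing here is wrong. A short pre-specified set containing baseline pain, demographics and site is defensible, and no rule makes every risk factor in a background section a covariate. The article never says that these factors predict pain over and above pre-surgery pain, which is adjusted for and may already carry part of their signal. At the planned 1.0-point difference the gain is only 0.6 to 1.5 percentage points of power. All of this stands, and it limits the point to an improvement.

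The reply also holds for the decay model. Three scores acting on initial value, rate and asymptote could add up to 3 x 3 = 9 parameters and put convergence at risk. Nor should the choice between separate anxiety and depression scores and a composite depend on the observed collinearity, since that adds a data-driven step to the primary analysis.

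A reader might infer something stronger: that the omission biases the primary comparisons, or that protection against chance imbalance is lost. The documents do not support this. Allocation is randomised, so omitting a baseline covariate from a linear model leaves the estimate unbiased and the test valid. Sex is stratified. Baseline pain, age, race/ethnicity and site are adjusted for, and any imbalance shared with baseline pain is partly removed.

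What the reply does not remove is that the article gives a closed list for all regressions, holds scores it calls predictive, and gives no reason for leaving them out.

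**Conclusion.** The point holds as a modest, inexpensive gain in precision. The primary analysis as written is valid. Under an assumed extra R2 of 5% to 15%, the SE of a 100 v 100 comparison falls by about 2.5% to 8%. Power moves by under two points at the planned 1.0-point difference, and by roughly two to six points at an assumed 0.7. The result rests on that R2 range, on SD 1.8 as the residual SD and on two-sided 0.05. If baseline pain already absorbs most of the psychosocial signal, the gain is smaller. No primary conclusion is shown to be at risk, and the gain for Hypothesis 1 has not been quantified.

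**What to change.** Before unblinding, extend the pre-specified covariates of the linear 3-month models (Hypotheses 2 and 3) and of the acute GEE model by three continuous T1 scores:
- one distress composite of PROMIS anxiety and PROMIS depression, with its formula fixed in advance (for example the mean of the two standardised scores)
- the Adolescent Sleep Wake Scale score
- the parent PHQ-4 score

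State that these terms are not required in the exponential-decay mixed model.

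The cost is a wording change and about three degrees of freedom, out of about 200 completers for Hypothesis 2 or 400 for the four-arm and pooled models. No new data are needed. Non-compliance with the baseline assessment is already a ground for removal from the study, so missing values in these scores should be few.

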### Secondary analyses

*Secondary efficacy outcomes:* Additional covariates adjusted regression models will examine differences in secondary acute outcomes (opioid use; T2), and secondary chronic outcomes (HRQL, anxiety, depressive symptoms, sleep quality, opioid misuse; T3) between the relevant treatment arms (as noted in primary analyses).

*Exploratory analyses:* Additional logistic analyses will compare rates of CPSP, a binary variable based on pain intensity and HRQL, at 3 months and 6 months in youth receiving combined pre- and post-operative CBT (arm 4) compared to arms 1, 2, and 3. We will also explore extent through which acute post-operative pain intensity and interference (T2) as well as changes in psychosocial factors (sleep quality, anxiety, and depression; T2-T4 relative to T1) exert their influence on (i.e., mediate) change in pain intensity, HRQL, and pain interference at 3 months follow-up using a structural equation modeling (SEM) approach.

Effect modification will be examined through regression models with interactions and subgroup analysis testing whether there are differential intervention effects across sex, racial, and ethnic groups on primary and secondary acute and chronic outcomes.

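### The covariate rule for all regression models names baseline pain intensity but not the outcome's own baseline, so the interference and secondary-outcome models lose precision that data already collected could supply

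*Protocol article*

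**What the plan says.** The Data analysis section of the protocol article states: "All regression analyses will adjust for a priori identified demographic variables (age, sex, race/ethnicity), prognostic covariates (pre-surgery pain intensity), and study site". Beyond the demographic variables, the list therefore holds only "prognostic covariates (pre-surgery pain intensity), and study site". The section then makes interference a primary outcome with its own models: "Separate models will be conducted to analyze pain severity and pain interference (primary outcomes").

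The Covariates section names a wider set of baseline pain measures: "adolescents will report on pre-surgery pain severity and interference using the 7-day recall version of the Brief Pain Inventory".

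The Secondary analyses section adds no outcome-specific baseline. It refers only to adjusted models, first for acute opioid use ("Additional covariates adjusted regression models will examine differences in secondary acute outcomes (opioid use; T2") and then for "secondary chronic outcomes (HRQL, anxiety, depressive symptoms, sleep quality, opioid misuse; T3"). Table 3 ticks T1 for the instruments behind every one of these outcomes, and the Assessment plan places T1 before randomisation.

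**The concern.** An outcome's own baseline is usually its strongest single predictor. Here the only baseline clinical measure in the stated list is pain intensity. That is the natural baseline for the severity models, but only a proxy for interference and a more distant one for HRQL, mood, sleep and opioid misuse.

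Two things are at stake. The first is precision: residual variance that could be explained stays in the error term. The second is chance imbalance. Randomisation is stratified by sex only (Trial design and randomization), so an accidental difference between arms in, say, baseline interference is corrected only so far as it tracks pain intensity.

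The article also disagrees with itself. One section presents baseline interference as a covariate, and the section that fixes the models leaves it out.

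**Working it through.** **Does intensity cover interference?** No. The Secondary analyses section lists them as different variables in one phrase: "change in pain intensity, HRQL, and pain interference at 3 months follow-up". The list in Data analysis therefore contains baseline intensity and not baseline interference.

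**Are the own-baseline values available?** Interference: yes, by the 7-day recall BPI (Covariates). HRQL, anxiety, depression, sleep quality and opioid misuse: yes, at T1 (Table 3). Opioid use also has a T1 tick, but the acute outcome is a count of days over 14 days of monitoring, so that T1 value is not a like-for-like baseline. The Patient Global Impression of Severity has no T1 value, but it is not among the outcomes named for analysis.

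**The plan's own figure.** The article gives no figure for the gain from covariates. The nearest is the sample size for the chronic pain outcomes: difference 1.0, SD 1.8, 80% power, two-sample t test, 35 per arm. Alpha is not stated. Taking 0.05 two-sided, n = 2 × (1.960 + 0.842)² × 1.8² / 1.0² = 50.9, so 51 per arm (52 with the exact t test). The 35 is not reproduced. That is a separate matter and nothing below depends on it. The target of 400 completers at 1:1:1:1 gives about 100 per arm, which is used below.

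**Gain for 3-month mean interference.** Assumptions, none from the documents:
- r = correlation of baseline interference with 3-month interference, 0.3 to 0.6
- a = correlation of baseline severity with baseline interference, 0.5 to 0.8
- baseline severity predicts 3-month interference only through baseline interference, so its correlation with the outcome is a × r

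Residual variance, as a fraction of the total:
- intensity only: 1 − (a·r)²
- with own baseline: 1 − r² (under the third assumption, keeping intensity in the model leaves this unchanged)

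| r | a | intensity only | with own baseline | ratio | n per arm, 80% power | power at 100 per arm |
|---|---|---|---|---|---|---|
| 0.3 | 0.8 | 0.942 | 0.910 | 0.966 | 48 to 47 | 98.2% to 98.5% |
| 0.5 | 0.8 | 0.840 | 0.750 | 0.893 | 43 to 39 | 99.0% to 99.5% |
| 0.5 | 0.5 | 0.938 | 0.750 | 0.800 | 48 to 39 | 98.2% to 99.5% |
| 0.6 | 0.5 | 0.910 | 0.640 | 0.703 | 47 to 33 | 98.5% to 99.8% |

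The last two columns use difference 1.0, SD 1.8, two-sided 0.05 and the normal approximation. The cut in residual variance runs from about 3% to about 30%.

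**Second set of assumptions, as a check.** Let severity have its own correlation c with the outcome, and fix the correlation between the two baselines at 0.6. Then R² = (r² + c² − 2·r·c·0.6) / (1 − 0.36).
- r = 0.4, c = 0.25: residual 0.938 to 0.840, a cut of 10%
- r = 0.5, c = 0.30: residual 0.910 to 0.750, a cut of 18%
- r = 0.6, c = 0.35: residual 0.878 to 0.640, a cut of 27%

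These lie inside the first range.

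**A smaller difference.** Hypothesis 3 sets combined treatment against single-phase arms, where the contrast could be below 1.0. Assume 0.5 points, SD 1.8, 100 per arm and the middle case just above. The standard error is 1.8 × √(0.910 × 2/100) = 0.243 with intensity only and 1.8 × √(0.750 × 2/100) = 0.220 with both. Power rises from about 54% to about 62%.

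**Chance imbalance.** Adjusting for intensity leaves a fraction 1 − a² of the variance of baseline interference unaccounted for: 1 − 0.8² = 0.36 to 1 − 0.5² = 0.75. The imbalance is partly corrected, not ignored.

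**The case against.** The strongest reply has four parts.

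1. *The Covariates heading already names interference, so it may be intended.* This stands in part. A reader might infer that baseline interference was deliberately excluded; the article does not show that. It shows two sections that do not agree.

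2. *For secondary outcomes the article is merely silent, and the analysis plan may add T1 scores.* The sentence in Data analysis does not forbid further covariates. But it is not silence either: it states a list for all regression analyses. A plan that follows it literally carries the gap forward.

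3. *The variance formula does not reach everything.* This stands. The primary acute outcome is an individual rate of recovery from an exponential decay model. A decay rate has no pre-surgery value, and the formula does not apply to it. It fits 3-month mean interference directly, the acute GEE analysis at best approximately, and a binary misuse outcome not directly. No size has been worked out for any secondary outcome.

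4. *The gain may be small.* This stands for the planned contrast. Major surgery intervenes, adolescents with diagnosed chronic musculoskeletal pain are excluded, and baseline uses a 7-day recall while outcomes use the 24-hour version. Each could weaken the baseline-outcome correlation and push the gain towards the low end.

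**Conclusion.** The point holds as one about efficiency and consistency. As written, the covariate rule omits the own baseline from the interference and secondary-outcome models although the values are collected before randomisation, and it does not match the Covariates section.

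For 3-month mean interference the loss is a residual variance that could be about 3% to 30% lower, resting wholly on assumed correlations. At about 100 completers per arm this adds only 0.3 to 1.3 percentage points of power for a 1.0-point difference. It matters more if the true contrast is smaller.

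Two stronger readings are not supported. A reader might infer that the treatment comparison is biased; under randomisation, leaving out a baseline covariate does not do that. A reader might also infer that the interference comparison is put at risk; for the planned 1.0-point difference the calculation shows otherwise.

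**What to change.** Reconcile Data analysis with Covariates before unblinding. Keep the existing list, including pre-surgery pain intensity, and add a sentence saying that each model also adjusts for the T1 value of its own outcome where one is collected:

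- **Interference:** baseline BPI interference in the 3-month linear regressions and the acute GEE, and as a prognostic covariate in the decay model where it applies.
- **HRQL, anxiety, depressive symptoms, sleep quality:** the T1 score of the same instrument.
- **Opioid misuse:** T1 misuse, if it is frequent enough at baseline for a stable fit. The article gives no rate.

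The own baseline should be added to pain intensity, not put in its place, since pain intensity is already a prespecified prognostic covariate.

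The cost is small: no new data, one more covariate per model, and a stated way of handling missing T1 values.
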